### Ethics considerations

All participants provide informed consent for the participation of themselves and their infants. The consent clarifies that the decision whether or not to participate in the study will not in any way affect usual care, and that participants are free to withdraw from the study at any time. Participants who are excluded due to current psychiatric condition are referred for treatment at the Centre for Women’s Mental Health of the RWH. Any changes in protocol are reported to and approved by the RWH Human Ethics Committee before implemented, and are updated on trial registration.

Adverse events are monitored during each assessment time point by the researcher who conduct the telephone interview. Further, participants are asked to report to the research team immediately if they experience unwanted adverse effects during participation. These events are recorded and included in human research ethics reports.

All data are stored with password protection. Each participant is assigned a numeric code. Personal identifiable information such as names and addresses, are stored separately from the research data. The file linking the numeric code to individual participants is password-protected, and only accessible to individuals listed on the human research ethics application. A data monitoring committee was not used due to limited funding.

Results will be disseminated in peer-reviewed publications, scientific conferences, and via community media outlets (e.g., newspaper articles). If findings are positive, we will seek opportunity to further evaluate the effectiveness of the intervention in clinical settings with the goal of eventual implementation.

### Statistical analyses and power

All analyses will be conducted on an intention-to-treat basis. Missing data is expected in a longitudinal design, and will be addressed using multiple imputation or full information maximum likelihood.

Descriptive statistics will provide information about the feasibility and acceptability of the program (Aim 1), including metrics of recruitment, dropout, email opening rates, patient satisfaction, and qualitative feedback.

To examine group differences in primary and secondary outcomes at each post-baseline time point (Aim 2), multiple regression analyses will be conducted with treatment condition (along with relevant covariates) as the independent variable, and the outcome of interest as the dependent variable. Effect sizes along with 95% confidence intervals will be calculated for the change across time (e.g., pre- vs post-intervention) and for group differences at each time point. The proportion of women meeting diagnostic criteria for Insomnia Disorder, and those above threshold for clinically-significant insomnia symptoms at each time point will also be described.

Changes in outcomes over time in both the overall sample, and the differential change trajectories between treatment conditions will be further explored using mixed effects models. Potential predictors of treatment response will be incorporated as relevant time-invariant and/or time-varying covariates in these models, so their effects on change trajectories can be examined.

Assuming 5% missing data at T1 and 15% at each follow-up [7], the proposed sample size of 150 is powered at 80% (two tailed α = 0.05) to detect a moderate sized difference (*d* = 0.5); moderate to large sizes are expected for primary outcomes [20].

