### Measurements

Text below summarises measurements used in this study, and specific details on each measure can be found in the Additional file 1. Table 2 shows when each measure is administered. As different factors contribute to maternal sleep characteristics during pregnancy and postpartum periods, we include 2 primary endpoints: T2 as the pregnancy endpoint, and T6 (immediately post-intervention) as the postpartum endpoint.

**Table 2 Tab2:** Timing of Measurements

Name of Measure	Pregnancy		Postpartum					
	T1	T2	T3	T4	T5	T6	T7	T8
Structured Interviews								
M.I.N.I. International Neuropsychiatric Interview	X							
Duke Structured Interview for Sleep Disorders	X	X^a^		X^a^	X^a^	X^a^	X^a^	X^a^
Primary Outcomes								
Insomnia Severity Index	X	X		X	X	X	X	X
PROMIS Sleep Disturbance - SF	X	X		X	X	X	X	X
Client Satisfaction Questionnaire, Program Feedback						X		
Secondary Outcomes								
Consensus Sleep Diary (adapted)	X	X		X	X	X	X	X
PROMIS Sleep Related Impairment - SF	X	X		X	X	X	X	X
PROMIS Depression – SF	X	X		X	X	X	X	X
PROMIS Anxiety – SF	X	X		X	X	X	X	X
EQ-5D-5 L	X	X		X	X	X	X	X
Dyadic Adjustment Scale-4	X	X		X	X	X	X	X
Prenatal Attachment Inventory	X	X						
Mother to Infant Bonding Scale				X	X	X	X	X
Adult Attachment Style Questionnaire – Short Form	X						X	
Parental Reflective Functioning Questionnaire							X	X
Emotional Availability Scale (25-min videotaped)						X	^b^	^b^
Strange Situation Procedure (25-min videotaped)							X	
Other Factors								
Ford Insomnia Response to Stress Test	X							
Credibility Expectancy Questionnaire	X							
Demographic and Obstetric Information	X			X		X	X	X
Brief Infant Sleep Questionnaire				X	X	X	X	X
PROMIS Instrumental and Emotional Support – SF	X	X		X	X	X	X	X
Dysfunctional Beliefs and Attitudes about Sleep Scale	X	X		X	X	X	X	X
Glasgow Sleep Effort Scale	X	X		X	X	X	X	X
Reduced Morningness and Eveningness Questionnaire	X	X		X	X	X	X	X
Intervention Adherence and Usefulness		X		X	X	X		
Australian Eating Survey	X					X		
Medical Records Extraction						X		

*Note. X* Measure administered at that time point; *SF* Short form; ^a^Insomnia Module only; ^b^ not administered, but coded from the Strange Situation Procedure

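### The visit-by-visit primary regressions do not fix the T1 value of the outcome as a covariate; doing so is a free gain in precision, not a repair of validity

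*Protocol article*

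**What the plan says.** Under Statistical analyses and power, the group comparison for Aim 2 is made at each post-baseline time point: "multiple regression analyses will be conducted with treatment condition (along with relevant covariates) as the independent variable". The covariates are not listed in that section. The longitudinal model comes second: "differential change trajectories between treatment conditions will be further explored using mixed effects models". Missing data are to be handled by multiple imputation or full information maximum likelihood.

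Under Other measures, infant sleep and social support are named as covariates, and infant feeding for attachment outcomes. Table 2 schedules infant sleep from T4 onwards, so it does not exist at T2.

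Table 2 schedules both primary instruments, the Insomnia Severity Index and "PROMIS Sleep Disturbance - SF", at T1. The note to Table 1 places the T1 assessment before the intervention. The Measurements section sets T2 and T6 as the primary endpoints. The description of randomisation gives random block sizes and names no stratification factor.

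**The concern.** The pre-intervention value of the same scale is usually among the most useful covariates for a later score, and it cannot be affected by treatment. Here it is scheduled for every participant, yet the text fixes only the treatment term. If T1 stayed out of the model, the T2 and T6 contrasts would have wider intervals than the collected data allow. A chance difference between arms in baseline insomnia would also go unadjusted, and the article names no stratification factor that would limit it. An open covariate set further leaves a choice to the analyst on the primary result.

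A related point is missing outcomes. Full information maximum likelihood in a regression for one visit gains nothing for a woman whose only missing value is that visit's outcome, unless her other visits enter the likelihood. The article does not say whether they do.

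**Working it through.** **Inputs from Statistical analyses and power.** "the proposed sample size of 150 is powered at 80"%; "two tailed α = 0.05"; "to detect a moderate sized difference" (d = 0.5); "Assuming 5% missing data at T1 and 15% at each follow-up". Allocation is 1:1 (Design).

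**Assumption.** The correlation r between the T1 value and the later outcome is not given. The range 0.2 to 0.6 is shown.

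**Step 1: reproduce the plan's figure.** For an unadjusted two-group comparison of means, the normal approximation needs 63 per arm, or 126 in total; 126 / 0.85 = 148.2, rounded up to 149. The t-based version needs 64 per arm, or 128; 128 / 0.85 = 150.6, rounded up to 151. Conversely, 150 × 0.85 = 127.5 analysed gives 80.0% power (noncentral t) or 80.6% (normal). The stated 150 and 80% therefore reproduce with no baseline adjustment.

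**Step 2: add the T1 value.** Adjustment multiplies the residual variance by 1 − r², so the effective standardised difference is d / √(1 − r²). The noncentrality is that value × √(N/4), where N is the total analysed.

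Example, r = 0.5, N = 127.5: 0.5 / √0.75 = 0.577; 0.577 × √31.875 = 3.26; power 89.9%.

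**Step 3: two ways of treating missing T1 values.** If they are imputed, N stays near 127.5. If those women are dropped and the two losses are independent, N = 150 × 0.95 × 0.85 = 121.1.

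| r (assumed) | Residual variance | Power, N = 127.5 | Power, N = 121.1 |
|---|---|---|---|
| unadjusted | 1.00 | 80.0% | – |
| 0.2 | 0.96 | 81.6% | 79.5% |
| 0.3 | 0.91 | 83.6% | 81.6% |
| 0.4 | 0.84 | 86.4% | 84.6% |
| 0.5 | 0.75 | 89.9% | 88.3% |
| 0.6 | 0.64 | 93.8% | 92.7% |

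The middle column treats imputed T1 values as if observed, so it is slightly favourable. At r = 0.2, dropping women without a T1 value would cost more than the adjustment gains (79.5% against 80.0%).

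**Step 4: what a longitudinal model adds beyond T1.** With 15% of outcomes missing and a correlation c between visits after T1 adjustment, the variance relative to complete data is 1 + (0.15 / 0.85) × (1 − c²). For complete cases it is 1 + 0.1765 = 1.176. At an assumed c = 0.5 it is 1 + 0.1765 × 0.75 = 1.132. The ratio 1.132 / 1.176 = 0.963, so the variance is about 4% smaller. Imputation that uses the other visits can recover much of the same gain.

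**The case against.** The strongest reply is that this is a condensed journal article. The T1 value is neither named nor excluded, the covariates it calls relevant may well include it, and a covariate list is commonly left to the analysis plan. That stands to this extent: no loss of precision is shown, and the loss is zero if T1 was intended. The list under Other measures is also weak evidence of exclusion, because the primary instruments are described in a different section. What remains is that the article does fix the form of the primary analysis and does name covariates, but not the one with the clearest case.

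Four stronger readings are tempting, and the document supports none of them.

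- **That the missing-data handling is ineffective.** Multiple imputation is one of the two permitted methods, and nothing keeps other visits out of either. The weakness applies only to maximum likelihood confined to one visit.
- **That within-arm change will serve as evidence of efficacy.** The plan does say "Effect sizes along with 95% confidence intervals will be calculated for the change across time (e.g., pre- vs post-intervention", and a change from 30 weeks' gestation to 6 months postpartum would mix treatment with childbirth and infant care. But the same sentence also gives effect sizes for group differences, and the hypothesis under Aims and hypotheses is between groups. Change scores are not called efficacy evidence.
- **That the mixed model must be primary.** Separate regressions at T2 and T6 are valid under randomisation, and Step 4 shows little further gain.
- **That T1 is known for every woman.** The plan itself assumes 5% missing there.

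It is also fair to say that a T1-to-T6 correlation may be low, because the article states that different factors drive sleep before and after birth. At r = 0.2 the gain is only 1.6 points.

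**Conclusion.** The point holds as a free improvement. The primary regressions at T2 and T6 do not fix the T1 value of the outcome, although it is scheduled before the intervention for both primary instruments. A reader might infer that the comparison is biased or the trial underpowered. Neither follows: randomisation keeps the unadjusted contrast unbiased, and the stated 80% reproduces without adjustment.

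If T1 was not intended, fixing it is worth from about 2 power points (r = 0.2) to about 14 (r = 0.6) at d = 0.5, provided missing T1 values are imputed. These sizes rest on an assumed correlation, the plan's 15% loss at follow-up and a common outcome variance. The protection against chance baseline imbalance, and the removal of an analyst's choice, do not depend on the exact correlation.

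**What to change.** State that the T1 value of the Insomnia Severity Index, or of PROMIS Sleep Disturbance, is a fixed covariate in the primary contrast for that instrument at T2 and at T6. State that missing T1 values are imputed, so that no randomised woman is dropped for lack of one. State that all visits enter the imputation model or, if full information maximum likelihood is used, the likelihood. A repeated-measures mixed model with pre-named contrasts at T2 and T6 is one way to do this; the per-visit regressions can stay if the three statements are made.

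The cost is a few sentences in the analysis plan, settled before outcomes are compared by arm. No new data are needed. If the analysis plan already says this, nothing changes.

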### Participants

Participants are 150 expectant mothers enrolled in Childbirth Education at the Royal Women’s Hospital (RWH), a centrally located public hospital specialising in women’s health in Victoria, Australia.

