#### Outcome measures

Feasibility is assessed using recruitment/dropout rates and email opening rates. Acceptability is assessed using the Client Satisfaction Questionnaire [30], and qualitative feedback from participants.

Efficacy outcomes are assessed with self-report instruments because subjective sleep complaints (and not objectively assessed sleep parameters) share strong association with mental health outcomes [7], and because insomnia is assessed and diagnosed via self-report. We selected instruments with strong psychometric properties.

The primary outcome is maternal sleep quality. Sleep disturbances during the perinatal periods are multifactorial, including symptoms of insomnia, as well as sleep disruptions related to fetus growth and infant care. Therefore, we operationalised the primary outcome into two domains: symptoms of insomnia assessed using Insomnia Severity Index [31], and overall sleep disturbance assessed using PROMIS Sleep Disturbance [32].

Secondary outcomes include Insomnia module on the DSISD [29] for Insomnia Disorder status and modified Consensus Sleep Diary [33] for self-report sleep patterns over the past week (e.g., sleep duration, onset latency, wake after sleep onset, daytime naps). Further secondary outcomes assess the impact of the intervention on maternal wellbeing. These include the following: maternal sleep-related impairment, assessed by PROMIS Sleep Related Impairment [32], maternal mental health, measured with PROMIS Depression and Anxiety [34], maternal health-related quality of life, assessed by EQ-5D-5 L [35], relationship satisfaction via the brief Dyadic Adjustment Scale-4 [36], and mother-infant relationship, measured with the Prenatal Attachment Inventory [37], the Mother to Infant Bonding Scale [38], the Emotional Availability Scales (4th Edition) [39], and the Strange Situation Procedure [40, 41].

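### The stated 80% power at two-sided 0.05 holds for one comparison, but the article declares four primary efficacy comparisons and gives no rule for success

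*Protocol article*

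**What the plan says.** Three parts of the protocol article bear on this point.

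- **Primary measures.** Under Outcome measures, maternal sleep quality is the primary outcome and is split in two: "we operationalised the primary outcome into two domains: symptoms of insomnia assessed using Insomnia Severity Index", and overall sleep disturbance on the PROMIS Sleep Disturbance form.
- **Primary time points.** Under Measurements: "we include 2 primary endpoints: T2 as the pregnancy endpoint, and T6 (immediately post-intervention) as the postpartum endpoint".
- **Analysis and power.** Under Statistical analyses and power, group differences in every outcome are examined by regression at each post-baseline visit. A single power statement follows: "the proposed sample size of 150 is powered at 80% (two tailed α = 0.05) to detect a moderate sized difference" of d = 0.5, assuming 15% missing data at each follow-up.

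The efficacy hypothesis under Aims and hypotheses is that the intervention group will report significantly better sleep quality. It does not say on which scale, at which time point, or on how many of the four results. Table 2 also lists client satisfaction and program feedback among the primary outcomes, but these are analysed descriptively, so the count of primary efficacy tests is four.

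**The concern.** Two scales at two time points make four primary tests, yet the sample size spends the whole 0.05 on one. With no success rule, one significant result among the four could be reported as confirming the primary hypothesis. The error rate behind that claim would be well above the 5% on which the power statement rests. If the intended rule is instead that all four must be significant, the error rate is safe but the probability of success is well below 80%. The article describes a superiority trial and says that positive findings would lead to further evaluation with a view to implementation, so what counts as positive matters.

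**Working it through.** **Inputs from the article.** N = 150, allocation 1:1, d = 0.5, two-sided α = 0.05, 15% missing at follow-up, two primary scales, two primary time points. The article gives no correlations. Those below are assumptions: 0.5 to 0.9 between scales at the same visit, 0.3 to 0.7 for the same scale across time, and the product of the two for different scales at different times.

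**Step 1: reproduce the stated power.** Evaluable women: 150 × 0.85 = 127.5, so n = 63.75 per arm. Noncentrality = d / √(2/n) = 0.5 / √(2/63.75) = 2.82. Noncentral t power for one test:

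| Two-sided α | Power |
|---|---|
| 0.05 | 80.0% |
| 0.025 | 71.0% |
| 0.0125 | 61.4% |

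The stated 80% is therefore correct for one test at the undivided 0.05. Compounding the 5% and 15% losses leaves 150 × 0.95 × 0.85 = 121.1 women and gives 77.9%, so there is no slack for a second test.

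**Step 2: success on any one of four tests, each at 0.05.**

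- Independent tests, two-sided: 1 − 0.95⁴ = 18.5%.
- Independent tests, false claims of benefit only: 1 − 0.975⁴ = 9.6%, against 2.5% for one test.

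**Step 3: correlated tests.** Four-variate normal simulation, 1,000,000 draws, d = 0.5 on all four for the power columns. The normal approximation used here gives 80.6% for a single test. Holm is applied at overall two-sided 0.05.

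| Between scales / across time | Any-one error, two-sided | False claim of benefit | Power, all four at 0.05 | Holm: at least one | Holm: average per test |
|---|---|---|---|---|---|
| 0.5 / 0.3 | 16.9% | 8.5% | 52% | 93% | 72% |
| 0.7 / 0.3 | 15.6% | 7.8% | 55% | 90% | 72% |
| 0.7 / 0.5 | 14.9% | 7.5% | 58% | 88% | 72% |
| 0.8 / 0.5 | 13.9% | 7.0% | 60% | 86% | 71% |
| 0.9 / 0.7 | 11.6% | 5.8% | 66% | 81% | 71% |

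**Step 4: what covariate adjustment could recover.** If a baseline covariate correlates r with the outcome, the effective effect size is d / √(1 − r²). At α = 0.0125 with 127.5 women, power is 66% for r = 0.3, 76% for r = 0.5 and 84% for r = 0.6. These values of r are assumptions. Both primary scales are collected at T1, but the article does not name the baseline score as a covariate.

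**The case against.** The strongest reply is that a multiplicity method is commonly left to a statistical analysis plan, which is not at hand. That is fair, and the absence of a named procedure is not the point here. The article itself fixes two primary scales, two primary time points and a sample size at undivided alpha. A later alpha split or an all-must-succeed rule would make the published 80% inapplicable per test or jointly.

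A reader might infer that no rule could keep both 5% and 80%. The documents do not support that. Holm holds the overall error at 5% and gives about 81-93% power for at least one success if d = 0.5 holds on all four. A fixed testing order would keep 5% overall and 80% for the first test. The article adopts neither rule, and it does not present its 80% as power for at least one success or for the first test in a sequence.

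A reader might also count all six post-baseline assessments on two scales as 12 primary tests and quote 1 − 0.95¹² = 46%. That does not hold either. Only T2 and T6 are named as primary endpoints, and repeated scores on related scales in the same women are not independent.

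Two further replies stand in part. The article justifies T2 and T6 by the different influences on sleep in pregnancy and postpartum. If each time point carried its own claim, the family would be two tests: at most 1 − 0.95² = 9.75% unadjusted, and 71% power per test at 0.025. The hypothesis, however, is worded as one claim. The article also expects moderate to large effects. A larger effect raises power (80% at 0.0125 if d = 0.6) but leaves the familywise error unchanged.

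**Conclusion.** The point holds. The power arithmetic is right for one comparison, but the article declares four primary ones and does not say which comparison or rule the 80% describes. Followed as written, any-one success carries a two-sided familywise error of about 12-17% (18.5% under independence) and a false claim of benefit in about 6-9% of null trials. All-four success has power of about 52-66%. These ranges rest on the assumed correlations; across that whole range the error stays above 5% and the joint power below 80%. The power figures further assume d = 0.5 on all four comparisons, 127.5 evaluable women and no covariate adjustment. What is established is a mismatch between the declared primary comparisons and the power statement, not that the sample size is inadequate under every possible rule.

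**What to change.** Before analysis, state one decision rule for the four primary tests. Holm at overall two-sided 0.05 is one example; a fixed testing order, or a rule that all four must be significant, is also possible if stated. Report the primary scales at T4, T5, T7 and T8 as secondary estimates with 95% confidence intervals.

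Restate the power to match the chosen rule. For d = 0.5, 127.5 evaluable women and no adjustment:

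- 80% for a single test at 0.05.
- Under Holm, 61% per test at the first step (0.0125), about 70-72% per test on average, and about 81-93% for at least one success if d = 0.5 holds on all four, with the correlations stated as assumptions.

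Naming the T1 score of each scale as a covariate would raise these figures at no cost in data collection. The cost overall is wording and a less favourable per-test power. No extra patients are needed.

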## Discussion

There is a significant gap between treatment availability, service delivery, and the high prevalence of sleep disturbances experienced by women during the pregnancy and postpartum periods. This study is a first step towards filling this gap, by establishing both short- and long-term efficacy of a sleep program tailored to the perinatal population. If successful, this light-weight and scalable intervention holds the potential of being incorporated into routine perinatal care and reach large numbers of women in the community. Midwives/nurses can be trained to incorporate the brief one-on-one support for program materials throughout routine clinical contact.

Further, this project focuses on early intervention and prevention, and takes a proactive approach by providing practical strategies for improving sleep during pregnancy, preparing mothers for significant sleep challenges during the postpartum periods. This has the potential to reduce adverse effects of poor sleep on women and their family.

Finally, sleep medication could lead to dependence in a long-term, and is often avoided by women and their physicians during the perinatal periods. This cognitive behavioural sleep intervention could help increase the awareness of non-pharmacological treatment among healthcare professionals and the public.

